## Retention

We will leverage the current approach which utilizes lay health workers and expert clients to ensure retention in the study and include additional strategies such as information leaflets about the importance of retention, appointment cards, motivational text messages, and phone calls (and home visits) to remind participants of appointments. All participants who miss study visits will be contacted.

| Table 3: Participant Timeline - Intervention Phase |                    |          |     |     |     |     |     |     |     |     |      |      |
|----------------------------------------------------|--------------------|----------|-----|-----|-----|-----|-----|-----|-----|-----|------|------|
|                                                    | Responsible person | Baseline | W 1 | W 2 | W 3 | W 4 | W 5 | W 6 | W 7 | W 8 | W 12 | W 24 |
| Screening of participants                          | LHW case manager   | X        |     |     |     |     |     |     |     |     |      |      |
| Informed Consent                                   | Research Assistant | X        |     |     |     |     |     |     |     |     |      |      |
| Enrollment in BSMART study                         | Research Assistant | X        |     |     |     |     |     |     |     |     |      |      |
| Intake Smoking Questionnaire                       | Research Assistant | X        |     |     |     |     |     |     |     |     |      |      |
| Follow-up smoking questionnaire                    | Research Assistant |          |     |     |     | X   |     |     |     |     | X    | X    |
| Stages of change                                   | Research Assistant | X        |     |     |     | X   |     |     |     |     | X    | X    |
| SBIRT Intervention                                 | LHW case manager   | X        |     |     |     |     |     |     |     |     |      |      |
| Breath CO                                          | Research Assistant | X        |     |     |     |     |     |     |     |     | X    | X    |
| Adherence to varenicline                           | Nurse prescribers  |          | X   | X   | X   | X   |     |     |     | X   |      |      |
| Adverse events monitoring                          | Nurse prescribers  |          | X   | X   | X   | X   | X   | X   | X   | X   |      |      |

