7. **Adherence to Medication**: Pill and counseling adherence will be assessed at Weeks 0, 1, 2, 4, 8, and 12. Pill adherence will be tracked by the following question at each medication visit: How many days in the last week did you take at least one of your study pills. Pill adherence will be defined by participant self-report of taking six or seven pills at week eight which coincides with their last receipt of varenicline.
8. **Adverse Event Monitoring** (Baseline, weekly for 4 weeks then every 4 weeks until week 12): Adverse events will be monitored at each study contact and classified and graded using the Common Terminology Criteria for Adverse Events and Common Toxicity Criteria provided by the National Cancer Institute. Our protocol for responding to Serious Adverse Events is summarized in the Human Subjects section.  
  
The 5 "A"s (SBIRT) Checklist and the Intake Smoking History Questionnaire will be administered at baseline for PLWH newly enrolling to HIV treatment and those currently on HIV treatment. A Follow-up Smoking Use Algorithm will be administered at baseline and at 4-, 12-, and 24-weeks of follow-up. The CO measurement will be obtained at baseline, 12 and 24 weeks of patient follow-up using coVita CO Smokerlyzer .

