## Data and safety monitoring plan

For all enrolled participants, study staff will collect information on events related to study involvement at each follow up visit including adverse events, perceived social harm, and events related to side effects related to quitting smoking. In addition to these events which we will monitor closely, we can expect that this population of HIV-infected men and women will experience adverse events unrelated to study procedures including new diagnoses of opportunistic infections, side effects from ART medications, hospitalization, and possibly death. Participant records will be carefully monitored internally by the study coordinator, project director, and investigators to ensure that no adverse events or social harms have been missed. We expect events to be minimal, but all will be documented, assessed for seriousness/severity and relatedness, carefully monitored, and managed by the onsite investigators. Our trial will adhere to the NIH adverse event reporting guidelines. All study-related adverse events will be reported to the MPI and to all regulatory bodies following the requirements of each committee.

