## Appendix C5: BSMART Side-effects Checklist

### BSMART Side Effect Checklist

|                            |                        |
|----------------------------|------------------------|
| Researcher ID:      | Participant ID: |
| District:           | Facility:       |
| Date: (dd/mon/yyyy) |                        |

|                                        |                                        |                                        |                                        |                                        |                                         |
|----------------------------------------|----------------------------------------|----------------------------------------|----------------------------------------|----------------------------------------|-----------------------------------------|
| Week Number:                    |                                        |                                        |                                        |                                        |                                         |
|  Week 1 |  Week 2 |  Week 3 |  Week 4 |  Week 8 |  Week 12 |

Ask the participant if he/she experienced these side effects in the last week. If participant endorses a side effect, then ask if it was mild, moderate or severe. If participant endorses a side effect, also ask how often it happened and if they took any medications for it or called a doctor. Make any notes at the back of this form. Use the following format: "Did you experience nausea in the last week?" If yes, continue with: "Would you say the nausea was mild, moderate or severe? How often did you experience nausea in the last week? Did you take any medications or call a doctor for your nausea in the last week?"

| Side Effect                    | None
(0)              | Mild
(1)              | Moderate
(2)          | Severe
(3)            | Not
Rated
(4)      | Missing
(99)          | Related to Medication:
A = None; B = Remote;
C = Possible; D = Probable;
E = Missing                                          |

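### The adverse-event schedule contradicts itself: the text requires a baseline assessment that neither Table 3 nor the side-effect form can record, and weeks 5 to 7 and 12 also conflict

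*Protocol*

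**What the plan says.** Three places in the protocol set the timing of adverse-event assessment in the intervention phase.

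- **Text.** Item 8 under Estimating process and outcome measures gives the schedule as "Baseline, weekly for 4 weeks then every 4 weeks until week 12". It then adds: "Adverse events will be monitored at each study contact and classified and graded".
- **Visit table.** Table 3 (Participant Timeline - Intervention Phase) has a row "Adverse events monitoring", assigned to nurse prescribers. It is blank at baseline, marked in every week from 1 to 8, and blank at weeks 12 and 24.
- **Form.** The checklist in Appendix C5 has tick boxes for weeks 1, 2, 3, 4, 8 and 12. It lists 40 named symptoms plus free entries and instructs: "Ask the participant if he/she experienced these side effects in the last week". Each symptom is also coded for attribution: "Related to Medication: A = None; B = Remote; C = Possible; D = Probable; E = Missing".

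Other sections tie monitoring to medication visits. Monitoring for adverse events places it at every pick-up, and Potential Risks to Subjects calls for a standardized questionnaire whenever medication is received. The Data and safety monitoring plan expects that "this population of HIV-infected men and women will experience adverse events unrelated to study procedures", and says that all events will be assessed for relatedness.

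**The concern.** A checklist that prompts for symptoms over the past week picks up whatever the participant has, whether or not the drug caused it. Several of the prompted items, such as headache, insomnia, back pain and fatigue, can be present in people who have taken no study drug, and the protocol itself foresees unrelated events, including ART side effects. The usual safeguard is a rating on the same form before the first dose, so that each later rating can be read as new, worse or unchanged.

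The text provides for an assessment at that point, but the two documents that staff use at the visit do not. If practice follows the table and the form, no such rating will exist. No later analysis plan can repair that, because the information was never collected. What is at stake is the interpretation of the varenicline side-effect data, including the adverse-event information that the DSMB section says is reviewed monthly.

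**Working it through.** No sample size, power figure or event count bears on this point, so the check compares the schedules week by week (baseline = week 0).

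| Source | Assessment weeks |
|---|---|
| Text, item 8 | 0, 1, 2, 3, 4, 8, 12 |
| Table 3, adverse-event row | 1, 2, 3, 4, 5, 6, 7, 8 |
| Appendix C5, week boxes | 1, 2, 3, 4, 8, 12 |

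**Differences**

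- In the text but not in Table 3: weeks 0 and 12.
- In Table 3 but not in the text: weeks 5, 6 and 7.
- In the text but not on the form: week 0 only. Otherwise the form matches the text.
- In Table 3 but not on the form: weeks 5, 6 and 7. On the form but not in Table 3: week 12.
- Weeks named by at least one source: 0, 1, 2, 3, 4, 5, 6, 7, 8 and 12, which is 10. Weeks on which all three agree: 1, 2, 3, 4 and 8, which is 5.

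**The pick-up rule as a cross-check.** Supply is weekly for four weeks and four-weekly for the next eight. Pick-ups at weeks 0, 1, 2 and 3 cover 4 × 1 = 4 weeks, and those at weeks 4 and 8 cover 2 × 4 = 8 weeks, 12 weeks in total. Item 7 of the same section confirms that the last receipt is at week 8. Monitoring at pick-ups therefore means weeks 0, 1, 2, 3, 4 and 8. It includes the first dispensing, which precedes the first dose. It does not produce visits at weeks 5 to 7 or week 12. So it matches none of the three schedules exactly, but it does support an assessment at baseline.

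**Could another instrument supply the pre-dose rating?**

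- Baseline information (item 1 of the same section) includes medical history, not symptom ratings.
- The nurse prescriber evaluates the participant and gives medical clearance before prescribing (Provision of varenicline), and Appendix C3 calls for history and chart review. Both concern suitability for the drug. Neither calls for the checklist to be completed.
- The intake questionnaire (Appendix B3) has no physical symptom checklist.
- The follow-up questionnaire (Appendix B4, item 8) rates some of the same symptoms, including nausea, headaches, insomnia and fatigue. It is used at weeks 4, 12 and 24, after dosing has begun, and is skipped by participants who report no quit of at least 24 hours.
- The control-phase timeline (Table 2) has no adverse-event row, and the checklist belongs to the varenicline tools, so untreated participants provide no parallel ratings.

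No structured pre-dose rating of the checklist symptoms is therefore provided for anywhere except in the text of item 8.

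**The case against.** The strongest reply has four parts.

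1. *The text requires the baseline assessment, and nothing says that the table and form override it.* This is fair as a reading of intent. The pick-up rule and the questionnaire at each receipt of medication point the same way. But the form has nowhere to record the assessment and the table does not schedule it, so compliance would depend on staff noticing the text.
2. *The form already deals with attribution.* Each item carries a relatedness code that includes None and Remote, and the Data and safety monitoring plan requires relatedness to be assessed. This stands and limits the consequence. A reader might infer that every symptom present before treatment will be counted as a varenicline side effect. The documents do not support that: a nurse can code such a symptom as unrelated, and no section says that every endorsed item is counted. What remains is that the code depends partly on whether the symptom preceded dosing, and the form does not record this.
3. *Pre-treatment clinical information exists.* It does, through history, chart review and the nurse's evaluation, and it will inform the judgement. It is not a rating on the same items with the same recall period.
4. *Side-effect rates are neither a primary nor a secondary outcome, and counting rules belong in an analysis plan.* Both statements are correct, and the absence of a counting rule is not criticised here. The point concerns data collection, which an analysis plan cannot supply afterwards.

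A reader might also take the Data and safety monitoring plan to predict a heavy load of background events. It does not: it says that unrelated events can be expected and also that events should be minimal.

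**Conclusion.** The contradiction is established from the documents alone. The text, Table 3 and Appendix C5 give three different schedules. They differ at baseline, at weeks 5 to 7 and at week 12.

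The consequence is moderate and conditional. If staff follow the table and form, symptoms that preceded varenicline cannot be reliably told apart from new or worsened ones, attribution rests on the nurse's judgement and the participant's recall, and side-effect frequencies may be overstated. The direction is plausible, because a persisting symptom would be endorsed at week 1 whatever its cause.

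The size cannot be computed. It would need the background prevalence of each symptom, how symptoms cluster within a person, how many implementation participants take varenicline, and how often nurses code pre-existing symptoms as unrelated. The documents give none of these. An illustration that took the checklist items as independent and all 375 implementation participants as treated would not be an estimate, since varenicline goes only to those who are motivated and medically cleared.

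The abstinence endpoint is untouched. The point is still worth settling before participants start varenicline, because the fix is cheap then and the missing rating cannot be obtained afterwards.

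**What to change.** Reconcile item 8 of Estimating process and outcome measures, the adverse-event row of Table 3 and the week boxes of Appendix C5 to one schedule. This must settle weeks 5 to 7 and week 12 as well as baseline, since a baseline mark alone would leave the three sources in conflict. The schedule should also be checked against the statements that tie monitoring to each medication pick-up and each study contact. Which schedule applies is for the sponsor to decide.

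If the baseline assessment already written in item 8 stands, add a baseline box to Appendix C5 and a baseline mark to the adverse-event row of Table 3. Have the form completed before the first dose, at the evaluation the nurse prescriber already holds at baseline, so that later ratings can be compared with it.

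The cost is an edit to one table and one form, and one more completion of an existing form at an existing visit: a few minutes for each participant who is given varenicline.

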## Data Collection

### Clinical Data

Data will be collected directly using tablets with REDCap Mobile Device Applications. The study team will work with the ABLE program staff to electronically extract all clinical and laboratory measurements longitudinally from the Integrated Patient Management System (IPMS) and the Patient Information

Management System (PIMS); the two main EMR systems used in Botswana and supported by BUMMHI, UMB's affiliate organization and BSMART study partner. Based on our experience, we anticipate high data quality as part of the ABLE program. All study sites will be connected by telephone and e-mail. Data will be extracted directly into a REDCap database (hosted by BUMMHI) by study personnel and immediately available for viewing by the study coordinator and data manager. Data checks will be put in place to verify completeness for each site (against IPMS, PIMS) and to check for data errors, using modifications of automated checks. Computer programmers in Botswana and Baltimore will evaluate the database and check for inconsistencies and missing data on an ongoing basis, and queries will be directed back to each site to maintain data quality.

#### Qualitative Data

|                               | Data Collector                        | Participants                            | Timing                                |
|-------------------------------|---------------------------------------|-----------------------------------------|---------------------------------------|
| Telephone Interview           | Investigators/
Research Assistants | Implementation
Leaders               | 3-6 months into intervention
phase |
| Focus Group Discussions       | Investigators/
Research Assistants | Lay Health Workers
Nurse Prescribers | Month 3 of intervention phase         |
| Semi-structured
Interviews | Investigators/
Research Assistants | Lay Health Workers                      | Week 24 of study participation        |

#### Costing Data

|                | Data Collector              | Timing                 |
|----------------|-----------------------------|------------------------|
| Fixed Costs    | Graduate Research Assistant | Baseline               |
| Variable Costs | Graduate Research Assistant | Week 12 then quarterly |

#### Process Variables

| Tool                                              | Data collector                        | Timing                                 |
|---------------------------------------------------|---------------------------------------|----------------------------------------|
| Activity Logs                                     | Research Assistant/ LHW               | Monthly during intervention
phase   |
| 40-item Program Sustainability
Assessment Tool | Investigators/ Research
Assistants | Intervention and
maintenance phases |

## Power and Sample size

Our sample size is based on the hypothesis that interventions will have a substantial impact on primary endpoints compared to the control phase (Figure 5).

**Main effect:** Based on a meta-analysis of 24 randomized controlled trials in LMIC, smoking abstinence at 6 months follow-up ( $P_{\text{control}}$ ) for usual care averages 10% (range, 8% to 14%). Assuming withdrawal from trial follow-up or loss to follow-up to be 5%, our sample of 25 PLWH per cluster per period has power of 87% to detect at least 10% increase (main effect,  $\Delta = (P_{\text{implementation}} - P_{\text{control}})$ ) in the primary endpoint at six months with the assumption that the event rate for those in control phase is 10% and two-sided alpha at intra-cluster correlation of 0.02.

[figure not shown]

Fig 5. Power to detect primary endpoint, main effect versus standard of care (SOC)

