- ii. Effectiveness is defined as a 7-day biochemically verified point prevalence abstinence from combustible tobacco products at 6 months using CO Check+. Our sample size (n=750 participants) has sufficient power to show at least 8% increase in a clinical effectiveness endpoint in the implementation group relative to standard of care (SOC) in the control group.
- 2. To assess the Adoption and Implementation of BSMART indexed by quality and consistency of intervention delivery.
  - i. identify how BSMART can be tailored to the network of HIV clinics in Botswana for adoption and implementation fidelity,
  - ii. foster comparison across clinical sites, and
  - iii. inform the development of activity logs to track implementation strategies.
- 3. To assess whether the intervention becomes Maintained as part of routine practices over time across HIV care facilities.
  - i. determine the extent to which the core components of BSMART and implementation strategies continue to be delivered and are maintained over time with fidelity and
  - ii. using the Program Sustainability Assessment Tool (PSAT), determine how organizational capacity and infrastructure to deliver BSMART are maintained, including partnerships, networks, and coalitions.
- 4. To determine the preliminary cost-effectiveness of BSMART - the incremental net monetary benefit at 6 months of follow-up in order to compare the value of BSMART to standard of care (SOC).

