## Methods

### Study Design

We will utilize a stepped wedge cluster randomized trial to implement BSMART. BSMART will be sequentially rolled out to 15 participating HIV treatment and care facilities assigned in three steps (Table 1). Each step will provide data for a 12-month control/pre-implementation, a 12-month implementation, and a 12-month maintenance period. We will stratify Botswana's HIV treatment and care facilities into three levels of facilities. We will randomly assign each of the three levels of facilities to one of three study steps. Each step will comprise (i.e. have representation) from three levels of facilities, giving each level of facilities the same probability of beginning the intervention at any step). We choose this design to:

- 1) minimize the practical, logistical, and financial constraints associated with large-scale project implementation,
- 2) control for the effect of time, and
- 3) ensure that all HIV treatment and care practices will eventually offer the intervention and assess maintenance.

The study will screen approximately 6,900 HIV-infected patients and we expect to enroll 750 eligible participants, 375 of whom will participate in the pre-implementation phase and 375 of whom will participate in the implementation phase across three waves of implementation at five facilities each.

| Table 1: Time Periods for Stepped Wedge Implementation |                                                  |         |                |                |                |             |
|--------------------------------------------------------|--------------------------------------------------|---------|----------------|----------------|----------------|-------------|
| Steps                                                  | Total Number of Participants                     | Year 1  | Year 2         | Year 3         | Year 4         | Year 5      |
| 1                                                      | 5 facilities, n=250 PLWH (1DH, 2 PHs, 2 clinics) | Control | Implementation | Maintenance    |                |             |
| 2                                                      | 5 facilities, n=250 PLWH (1DH, 2 PHs, 2 clinics) |         | Control        | Implementation | Maintenance    |             |
| 3                                                      | 5 facilities, n=250 PLWH (1DH, 2 PHs, 2 clinics) |         |                | Control        | Implementation | Maintenance |

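### The stated 87% power is not that of the Table 1 layout once calendar time is controlled (about 80% for 10 points, 63% for 8), and the 8-point and 10-point power claims disagree

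*Protocol*

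**What the plan says.** The Power and Sample size section states that "our sample of 25 PLWH per cluster per period has power of 87% to detect at least 10% increase" in the six-month primary endpoint. The inputs are "the assumption that the event rate for those in control phase is 10" per cent, "two-sided alpha at intra-cluster correlation of 0.02" (no alpha value is given), and "Assuming withdrawal from trial follow-up or loss to follow-up to be 5" per cent.

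Objective 1.ii in the Rationale makes a different claim for the same trial: "Our sample size (n=750 participants) has sufficient power to show at least 8% increase in a clinical effectiveness endpoint".

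Study Design says that "BSMART will be sequentially rolled out to 15 participating HIV treatment and care facilities assigned in three steps" and that "we expect to enroll 750 eligible participants, 375 of whom will participate in the pre-implementation phase", with the other 375 in the implementation phase. In Table 1 each step has one control year followed by one implementation year: Step 1 in Years 1–2, Step 2 in Years 2–3, Step 3 in Years 3–4. Control of the effect of time is listed there as one of three reasons for the design.

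The Statistical Analysis for Study Objective 1 specifies random effects for facilities and periods and fixed effects for facility type. It names no fixed calendar-year term.

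**The concern.** In every facility the implementation year follows the control year, so a secular change in quitting is confounded with BSMART unless calendar time is modelled. Modelling it costs information. Year 1 contains only Step 1 control participants and Year 4 only Step 3 implementation participants. With a free effect for each year, those 2 × 5 × 25 = 250 participants, a third of the sample, say nothing about the intervention effect. A power figure that ignores this is too favourable for a time-adjusted analysis.

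The sponsor, funder and DSMB will read the trial's sensitivity from these two statements. If the true effect is 8 points and the analysis uses fixed years, the trial misses it more than one time in three, and a null result could be taken as evidence against BSMART.

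**Working it through.** **Inputs.** Control rate 10%, so 20% for a 10-point and 18% for an 8-point increase; ICC 0.02; 25 per facility per period less 5% = 23.75 (all from Power and Sample size, with the 8 points from the Rationale). 15 facilities in 3 steps of 5, two cells each (Study Design, Table 1). Alpha: two-sided 0.05, assumed. Power = Φ(difference/SE − 1.96).

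Average binomial variance s²: 10 points, (0.09 + 0.16)/2 = 0.125; 8 points, (0.09 + 0.1476)/2 = 0.1188. For 10 points, the facility variance is 0.02 × 0.125 = 0.0025, the cell residual 0.98 × 0.125/23.75 = 0.005158, and their sum, the cell-mean variance, 0.007658.

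**Reproducing 87%.**

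(a) 15 + 15 independent facility-periods, no time term. SE = √(2 × 0.007658/15) = 0.0320; power 87.9%. With the design effect on 25, 1 + 24 × 0.02 = 1.48: effective n per arm = 375 × 0.95/1.48 = 240.7, SE = √(0.25/240.7) = 0.0322, power 87.3%. For 8 points: 72–73%.

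(b) Complete wedge, every facility enrolling in all four years (15 × 4 × 25 = 1,500). Hussey–Hughes variance with I = 15, T = 4, U = 30, W = 350, V = 70: 15 × 0.005158 × (0.005158 + 4 × 0.0025) / (100 × 0.005158 + 250 × 0.0025) = 0.001028. SE 0.0321; power 87.7% (87.0% with pooled variance). For 8 points: 72–73%.

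**Table 1 with fixed calendar years.** The effect is estimated in Year 2 (Step 1 implementation minus Step 2 control) and in Year 3 (Step 2 implementation minus Step 3 control). Each contrast of five-facility means has variance 2 × 0.007658/5 = 0.003063. Step 2 enters both with opposite sign, so their covariance is −0.0025/5 = −0.0005. The variance of their average is (0.003063 − 0.0005)/2 = 0.001282, SE 0.0358. Generalised least squares on all 30 cells gives the same SE, and so does deleting the Year 1 and Year 4 cells.

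- 10 points: 0.10/0.0358 = 2.793; power **79.8%**.
- 8 points: SE 0.0349; 0.08/0.0349 = 2.292; power **63.0%**.
- Simulation with binary outcomes, 24 per cell: 82% and 63%, null rejection 4.9%.
- A t reference on an assumed 10–24 degrees of freedom: 71–76% for 10 points.
- 87% power needs about 11.2 points: s² = 0.1285, SE = 0.0363, (1.96 + 1.126) × 0.0363 = 0.112.
- 10 points over ICC 0.01–0.05: 83% to 70%. Over the protocol's control range of 8–14%: 84% to 72%.

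**Table 1 under other treatments of time.**

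| Model | 10 points | 8 points |
|---|---|---|
| Fixed calendar years | 80% | 63% |
| Linear time | 82% | 66% |
| Random year, SD 0.06 | 88% | 72% |
| Random year, SD 0.05 | 89% | 75% |
| No time term, independent facility-periods | 88% | 73% |
| No time term, constant facility effect | 97% | 88% |

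The year SDs are illustrative; the protocol states none.

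**The case against.** The strongest reply is that the 80% and 63% rest on a term the protocol does not print. The analysis section has random period effects and fixed effects only for facility type. On that text a reader can reach about 87% for 10 points with the planned 750: 87.9% with independent facility-period effects, or 87.7% with a random year effect of SD 0.06. This stands. One might infer that 87% corresponds to no analysis the protocol allows, or that the 8-point claim is simply false; the documents support neither. With no time term and a constant facility effect, power for 8 points is about 88%.

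What this reply does not do is rescue the pair of statements. The model that makes 8 points well powered gives 97%, not 87%, for 10 points. The independent facility-period basis has no time term, contrary to the design's stated aim, and treats a facility's two years as unrelated although the Standard of Care section calls each site its own control. The random-year route needs a year variance stated nowhere.

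Two further reservations are fair. Alpha is not printed: at two-sided 0.10, Table 1 with fixed years would give 87.5% and 74.1%. Figure 5 is not available here and may carry further assumptions. Finally, 80% for 10 points is a conventional target, so it does not follow that the trial is too small for the effect on which the power section sizes it.

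**Conclusion.** The point holds in conditional form. At two-sided 0.05, the printed 87% is not the power of the Table 1 layout when calendar time is controlled by fixed years (79.8%) or a linear trend (82.4%). For 8 points the corresponding figures are 63.0% and 66.0%. The 10-point figure falls further with small-sample degrees of freedom.

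Independently of the time model chosen, the two power statements do not fit together: each basis found that gives about 87% for 10 points at alpha 0.05 leaves 72–73% for 8.

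The sizes rest on the protocol's control rate, ICC and loss, on alpha 0.05, and on a facility effect that is constant over a facility's two years.

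**What to change.** In Power and Sample size, print the alpha value. Replace 87% with the power of the incomplete stepped wedge in Table 1 under a stated time-adjusted model: with fixed calendar years, about 80% for 10 points, 83% to 70% over ICC 0.01–0.05, and 84% to 72% over control rates of 8–14%. Say that small-sample degrees of freedom lower it.

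In the Statistical Analysis for Study Objective 1, name the same time term, so that the power and the analysis refer to one model.

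In Rationale objective 1.ii, replace the 8-point claim with the 10-point effect, or state about 63% power for 8 points under that model.

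The cost is protocol wording and a less favourable printed figure. Enrolment, design and conduct do not change.
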